#### Adherence to the intervention and evaluation

MANTRa is designed for flexible use (e.g. no predetermined order in which MANTRa workbook has to be worked through, modules may be omitted if not relevant for a specific patient). In order to assess general adherence to the MANTRa intervention, therapists will be asked to keep a written record of the main topics discussed / modules of the workbook addressed in each session. Additionally, the 8th and 16th therapy sessions will be audiotaped. The TAU group should reflect a representative treatment-as-usual setting; therefore, no specific regulations or strategies to assess adherence will be implemented.

In both groups, the therapist discusses the general conditions and the groundrules of psychotherapy in the first session, including procedures in case of short-term cancellation of appointments, illness, confidentiality, data protection, etc. In case of unexcused absence, the therapist contacts the patient to arrange a new appointment. In case of repeated cancellations, this will be discussed in the therapy with the patient in order to increase adherence.

In order to promote participant retention in research assessment, each participant will be invited personally by the research team. In both groups, patients will be contacted twice via telephone and afterwards once or twice via text message/email. If participants do not respond, their parents will be contacted to establish contact with the participant. Reminders will be sent if questionnaires have not been completed in time. Furthermore, case managers are committed to this project and will further motivate the patients to participate in follow-up assessments.

#### Relevant additional care permitted during trial

In both groups, participants will be in regular medical care to monitor the physical health and weight gain provided by a case manager (child and adolescent psychiatrists or child and adolescent psychiatrists in training under supervision, psychologist), and will receive nutritional consultation by a dietician. Parents will be regularly included in the medical treatment provided by the case manager and will additionally be invited to participate in the parental skills training “SUCCEAT” which aims to reduce caregiver burden and supports parents in caring for a person with an ED [37–39].

During the course of this trial, the study participants will not be allowed to attend two different forms of individual psychotherapeutic treatment simultaneously. Participants will be encouraged to continue psychotherapy or start a new psychotherapy if they are still suffering from AN or another mental disorder after MANTRa or TAU had ended. Case managers will be responsible for ensuring appropriate follow-up treatment.

#### Criteria for discontinuing or modifying allocated interventions

AN symptomatology and medical risk will be monitored continuously by the case manager. MANTRa and TAU will be both suspended in case inpatient treatment becomes necessary due to worsening of AN symptomatology, i.e. further weight loss in an outpatient setting, as well as deterioration of medical parameters and/or somatic/psychiatric comorbidity. These criteria are in accordance with recommendations for starting inpatient treatment of the German guidelines for diagnosis and treatment of eating disorders [30]. After discharge, the intervention will be continued. Participants will be also allowed to ask for a change of the therapist, if the therapeutic relationship is experienced as not suitable for them.

### Outcomes

All outcome variables will be assessed prior to intervention start at baseline (T0) and after 12 months (T2). The primary outcome (ED psychopathology), comorbidities and quality of life will be additionally collected 6 months after baseline (T1) and at 18-month follow-up (T3) (see Fig. 1 for details). Self-report questionnaires will be administered online via ‘LimeSurvey’, while interviews will be conducted face-to-face or via telephone by trained professionals.

**Fig. 1 Fig1:**
[figure not shown]
Schedule of enrollment, interventions and assessments. ** T0 = baseline assessment, T1 = 6-month assessment, T2 = 12-month assessment, T3 = 18-month assessment

#### Primary outcomes: eating disorder psychopathology

Body Mass Index (kg/m^2^) at 12 months.Eating Disorder Examination (EDE) [40] global score at 12 months. The semi-structured EDE interview is gold standard in ED research. It comprises four subscales (dietary restraint, eating concern, weight concern, shape concern) and a global score assessing general ED psychopathology. The EDE has excellent reliability (total score: Cronbach’s α = .93); good convergent validity (.56 < r < .81) was observed with other measures of ED pathology [40]. Similar results were found in an adolescent population (Cronbach’s α = .93) [41]. Two psychologists trained and supervised in conducting the EDE interview by a senior clinical psychologist ([name]) will perform the interviews. They will not be blind to the intervention but are part of the independent research team and not involved in the clinical treatment and psychotherapy.Eating Disorder Inventory (EDI-2) [42] global score at 12 months. The EDI-2 is a self-rating questionnaire assessing various ED dimensions through 11 subscales (Drive for thinness, Bulimia, Body Dissatisfaction, Ineffectiveness, Perfectionism, Interpersonal Distrust, Interoceptive Awareness, Maturity Fears, Asceticism, Impulse Regulation and Social Insecurity) and a total score. The measure has excellent internal consistency (total score: Cronbach’s α = .90).

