**Methods/design:**

One hundred patients between 13 and 21 years who meet the inclusion criteria will receive 24 to 34 individual weekly MANTRa therapy sessions or weekly TAU sessions. Primary outcome variables will be BMI and eating disorder psychopathology 12 months after baseline. Further changes in central coherence, cognitive flexibility, emotion recognition, comorbid psychopathology (e.g. depression, obsessive-compulsive and anxiety disorders, non-suicidal self-injury), personality factors and therapeutic alliance will be assessed.

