
However, it is unclear whether the high acceptability, low dropout rates or improvements in ED psychopathology observed in adult patients receiving MANTRA [18, 19] can be transferred to adolescents with AN. This paper is a study protocol for a multi-center cohort study assessing the feasibility, acceptability and efficacy of an adapted version of the MANTRA treatment program for adolescents and young adults with AN (subsequently named “MANTRa”) compared to psychotherapeutic treatment as usual (TAU). We hypothesize that patients in the MANTRa intervention group will show a BMI increase and a reduction of ED symptoms at 12 months compared to baseline and that MANTRa will be superior to TAU with regard to BMI increase, ED psychopathology and treatment acceptability.

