#### Intervention group (MANTRa)

The MANTRa intervention (‘Maudsley Model of Anorexia nervosa treatment for adolescents and young adults’) is an adapted version of the original MANTRA treatment program for adult patients with AN and is designed as an outpatient manualized treatment program consisting of 20 weekly therapy sessions of approx. 50 min. followed by 4 monthly booster sessions. Patients with a more severe illness (one or more comorbidities, BMI below the 3rd sex and age-specific BMI percentile and illness duration longer than 1 year) will receive an extended version consisting of 30 weekly sessions, followed by 4 booster sessions. Whether a patient will receive the longer or shorter version will be decided according to the criteria mentioned above prior to the intervention start.

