The original workbook [17] was translated into German and had been adapted to the developmental level of adolescents in terms of language, design and content by our research team. A tabular description of the differences between MANTRA for adults compared to MANTRa for adolescents according to the TIDieR framework [31] is provided as supplementary material. For example, explanations for technical terms were inserted and a form of address customary for young people was used. In terms of content, we created three case vignettes representing typical adolescents suffering from AN, which are introduced in the first chapter and occur in every chapter explaining certain exercises. The case vignettes enable the patient to identify with adolescents who experienced similar events and who could serve as role models on the way to recovery. In chapter four, we changed nutritional recommendations according to suggestions of our dieticians who are experienced in the field of adolescent’s EDs (e.g. portion sizes are illustrated using the hand proportions and fists, not focusing on calories) and added information and exercises for managing binge eating and purging behavior. Dietological exercises of chapter four, such as the creation of a meal plan and nutritional recommendations are carried out by dieticians (see section ‘2.4.5. Relevant concomitant care permitted during trial’). BMI tables were replaced by BMI-percentile graphs. In chapter seven, which addresses emotions, we added the distress tolerance exercises from the Dialectic-Behavioral Therapy for Adolescents [32], because adolescents suffering from AN often engage in non-suicidal self-injury behaviors or experience emotion regulation problems [33]. Thus, adolescents need effective tools to help dealing with and expressing overwhelming emotions, as well as understanding the emotion regulation function of AN [34]. We also added a new chapter about social media and mobile applications to the workbook which was based on materials provided by South London and Maudsley NHS Foundation Trust [35], because social media platforms provide the opportunity and risk to communicate and exchange illness related as well as health-related thoughts known to be frequently used by adolescents [36]. Discussions about helpful and unhelpful aspects of social media platforms can be important for adolescents. Furthermore, we also adapted the design and layout of the workbook to make it more appealing for adolescents by creating each chapter in a different color and adding icons for better visual recognition of recurrent content (e.g. a letter icon for writing tasks or a question mark for reflection exercises). An overview of the chapters of the adolescent version of the workbook can be found in Table 1.

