
### Sample size

The sample size calculation was conducted with G*Power Version 3.1.9.2 and was based on the primary outcome analysis (difference in BMI, EDE total score and EDI total score between the baseline and 12-month follow-up assessment in the MANTRa intervention group). Based on previous studies, at least medium effect sizes (dz = 0.5) for the change in BMI and ED pathology can be expected [18, 67]. Using *t*-tests for paired samples, a sample size of 34 for the MANTRa group is needed to detect an effect size (dz) of 0.5 (alpha 5%) with a power of 80%. To account for a dropout rate of 25%, a total of 50 patients will be recruited for the MANTRa intervention group.

Furthermore, we plan to obtain the same number of patients (*N* = 50) for the control group. Sensitivity calculations revealed that differences in the primary outcome variables between the MANTRa and control group can be detected for small to medium effects (f = 0.14) (group x time interaction using general linear mixed models). Using multi-center recruitment, it is expected to reach the target sample size.

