### Statistical analysis

The primary statistical analysis will be based on the intention-to-treat principle, which means that participants will be analyzed in the group to which they were allocated irrespective of their compliance with the assigned treatment. Missing data will be imputed; the specific imputation model will be developed once the final data is available. *T*-tests for paired samples will be carried out for analyzing pre-post differences (T0-T2) in the three primary outcome variables (BMI, EDE, EDI-2). To account for multiple testing (three primary outcome variables) and the inflation of the Type I error rate, we will use Bonferroni correction to adjust the significance level (α = .017). Additionally, a completer analysis will be conducted as a secondary analysis. General linear mixed models will be used to measure effects between groups and over time (T0, T1, T2, T3) with using the treatment type (MANTRa vs. TAU) as between factor and assessment time (T0, T1, T2, T3) as within-factor. The treatment type x time interaction will indicate whether there is a difference in the course between the MANTRa and control group. Additional *t*-tests will be used to explore group differences between intervention (MANTR-a) and control group (TAU).

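### The primary weight outcome is raw BMI in 13–21-year-olds, tested as an uncontrolled change from baseline, so expected growth in the younger patients counts as treatment response

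*Protocol article*

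**What the plan says.** All references are to the protocol article.

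- **Outcome.** Under Primary outcomes, the weight measure is "Body Mass Index (kg/m^2^) at 12 months". Neither the primary nor the secondary outcomes name a percentile, standard deviation score or percentage of median BMI.
- **Population.** The Abstract (Methods/design) gives "One hundred patients between 13 and 21 years who meet the inclusion criteria".
- **Hypothesis.** The Introduction expects that "patients in the MANTRa intervention group will show a BMI increase and a reduction of ED symptoms at 12 months compared to baseline". It also expects MANTRa to be superior to TAU in BMI increase.
- **Primary test.** Under Statistical analysis, t-tests "for paired samples will be carried out for analyzing pre-post differences (T0-T2) in the three primary outcome variables (BMI, EDE, EDI-2") are run at a Bonferroni level of .017. The Sample size section places this comparison "between the baseline and 12-month follow-up assessment in the MANTRa intervention group", so the test has no control group, and no covariate is stated for it.
- **Effect size.** Under Sample size, "at least medium effect sizes (dz = 0.5) for the change in BMI and ED pathology can be expected". No mean change or SD in kg/m² is given.
- **Age-specific BMI elsewhere.** Under Intervention group (MANTRa), one criterion for the extended treatment version is "BMI below the 3rd sex and age-specific BMI percentile". In adapting the workbook for adolescents, "BMI tables were replaced by BMI-percentile graphs".
- **Group formation and adjustment.** Patients are assigned by centre and by existing psychotherapy (Assignment of intervention). Under Limitations, the groups will be compared on characteristics that include age, these will be added as covariates if needed, and group differences are to be read as observational.

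**The concern.** A sex- and age-specific percentile is needed only because the BMI expected of a healthy young person depends on age. The protocol accepts this when it grades severity and when it shows patients their weight, but its primary outcome goes back to kg/m² and no reason is given.

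The primary test compares the mean 12-month change with zero. For a 13-year-old, zero change in kg/m² is a loss against age norms, and staying on the same low percentile is a positive change. For a 20-year-old the two nearly coincide. The test has neither a comparator nor a covariate, so whatever growth is expected in the sample enters the estimated effect in full and in the favourable direction. A reader who takes a significant BMI increase as evidence of weight recovery could be misled.

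The comparison with TAU has a related weakness. The groups are not randomised. If they differ in age, they differ in expected growth, and this can appear as a difference in BMI course.

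**Working it through.** **1. The plan's own figure.** Inputs from Sample size: dz = 0.5, alpha 5%, power 80%. For a paired t-test the noncentrality is dz × √n and the critical value is t(1 − alpha/2, n − 1). With n = 34 the noncentrality is 0.5 × √34 = 2.92, the two-sided critical value is 2.03 and the power is 0.808. With n = 33 the power is 0.795. The stated 34 reproduces as a two-sided calculation.

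**2. Inputs for the growth check.**

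- From the documents: alpha = .017; n = 50 recruited; 25% dropout, so 50 × 0.75 = 37.5, taken as 37 completers.
- Assumed, not in the documents: growth of 0.3–0.7 kg/m² per year in younger patients and 0.1 in older ones; half the sample in each; SD of 12-month BMI change 1.5–2.0 kg/m².
- Mean increment over the sample: (0.3 + 0.1)/2 = 0.2 up to (0.7 + 0.1)/2 = 0.4 kg/m².

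**3. Chance of a significant result when growth is the only change.** Put dz = growth/SD into the same test at .017. The critical value is 2.50 for n = 37 and 2.47 for n = 50.

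| Mean growth (kg/m²) | SD | dz | n = 37 | n = 50 |
|---|---|---|---|---|
| 0.2 | 2.0 | 0.10 | 3.7% | 4.6% |
| 0.2 | 1.5 | 0.13 | 5.5% | 7.1% |
| 0.3 | 2.0 | 0.15 | 6.6% | 8.8% |
| 0.3 | 1.5 | 0.20 | 11.2% | 15.6% |
| 0.4 | 2.0 | 0.20 | 11.2% | 15.6% |
| 0.4 | 1.5 | 0.27 | 20.4% | 28.9% |

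These are two-sided rejection rates. The decrease tail contributes less than 0.2 percentage points in every row, so they are almost entirely significant increases. With no growth the rate would be 1.7%. As a share of the planned dz of 0.5, growth supplies 0.10/0.5 = 20% to 0.267/0.5 = 53%.

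**4. Between groups.** Assume that the yearly increment falls evenly from 0.4–0.6 kg/m² at age 13 to 0.1–0.2 at age 21. The bias in 12-month change is then (increment at 13 − increment at 21)/8 for each year of mean age difference.

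- Smallest case: (0.4 − 0.1)/8 × 1 year = 0.04 kg/m².
- Largest case: (0.6 − 0.1)/8 × 3 years = 0.19 kg/m².
- At an SD of 2.0 this is d = 0.02 to 0.09.

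An unadjusted t-test on the 12-month BMI level would be affected more. If BMI rises by 0.4 kg/m² per year of age (assumed), a gap of 1–3 years shifts the difference by 0.4–1.2 kg/m².

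**5. Whether the planned covariates solve it.** The paired test takes none, and none is stated for the additional t-tests. In the mixed model, a main effect of age shifts a patient's BMI equally at all visits. It therefore leaves age-dependent growth in the treatment × time interaction. Removing that needs a standardised outcome or an age × time term.

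**The case against.** Four objections deserve an answer.

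**The null is right for the stated hypothesis.** The Introduction hypothesises a BMI increase from baseline. If mean BMI truly rises, rejecting zero change is correct. A reader might infer from the table that the Type I error rate is inflated above 1.7%. The documents do not support that reading: the percentages describe how often a correct rejection would coincide with no gain against age norms. The objection stands, and the problem is one of interpretation.

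**The size could be pushed much higher.** Applying 0.7 kg/m² to every patient with an SD of 1.5 gives dz = 0.47 and rejection in 63% (n = 37) or 79% (n = 50) of trials. That treats a 20-year-old as growing like a 13-year-old. The eligible range of 13–21 does not support it, and the age mix is not given.

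**Age is already addressed between groups.** A reader might infer that age differences do bias the comparison and that the plan ignores them. Neither follows. The Limitations section names age as a possible covariate and calls group differences observational, and no document shows that the groups differ in age. What remains is that the adjustment is conditional and, as a main effect, incomplete.

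**Standardising does not rescue a one-arm test.** Regression to the mean, natural course and concomitant care remain in any pre-post change. This is true, but expected growth is the part that can be removed from data already in hand.

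**Conclusion.** The concern holds as a point about what the primary BMI result can show. Raw BMI change tested against zero, without a control group, counts expected growth in younger patients as treatment response. The protocol's own use of percentiles shows that an age-specific scale was available. The direction of the effect is clear.

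Its size is not. On a mean increment of 0.2–0.4 kg/m² and an SD of 1.5–2.0, about 4–20% (n = 37) or 5–29% (n = 50) of trials with no gain against age norms would show a significant BMI increase. An older sample would bring these figures down and a younger one would raise them.

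For the comparison with TAU, the documents support only that an age difference can bias the result. The bias in 12-month change is probably small. It would matter more for an unadjusted comparison of BMI levels, which the plan treats as exploratory.

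**What to change.** Define the primary weight measure as age- and sex-standardised BMI at T0 and T2: either BMI-SDS or percentage of the age- and sex-specific median BMI, from one named reference. Use it in both the paired test and the mixed model, and report raw BMI as a secondary outcome.

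If the registered primary outcome is not to be changed, prespecify the standardised analysis alongside raw BMI and base any conclusion about weight recovery on the standardised result.

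No new data are needed, since the sex- and age-specific percentile criterion already requires age, sex and BMI. The change is still more than a matter of wording. Recruitment began in April 2018 and the trial is registered, so a change of primary outcome must be documented and dated. The dz of 0.5 rests on previous studies and must be re-justified on the new scale. Results will be less directly comparable with adult studies, which the retained raw BMI covers.

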#### Secondary outcomes

Comorbid psychopathology: The State-Trait Anxiety Inventory (STAI) [43] is a self-rating questionnaire assessing anxiety. The STAI has excellent internal consistency (Cronbach’s α ≥ .89). Depression will be measured with the Beck Depression Inventory (BDI-2) [44], a self-rating questionnaire with excellent internal consistency (Cronbach’s α = .92) observed in an adolescent population [45]. The Obsessive-Compulsive Inventory Revised (OCI-R) [46] is a self-rating questionnaire for the assessment of obsessive-compulsive traits and symptoms. The German version demonstrated excellent validity and internal consistency (total score: Cronbach’s α = .86) for adults; no data are currently available for adolescents [46]. The STAI, BDI-2 and OCI-R will be completed by the participants. The presence of a comorbid psychiatric disorder (anxiety or obsessive-compulsive disorder, depression, non-suicidal self-injury, post-traumatic stress disorder) according to DSM-5 diagnostic criteria is diagnosed by a psychologist via a semi-structured clinical interview (Diagnostic Interview for Mental Disorders in Children and Adolescents; Kinder-DIPS) [47].Quality of life will be measured with the German version of the Inventory for Assessment of Quality of Life in Children and Adolescents (ILK) [48], a self-rating questionnaire with acceptable internal consistency (Cronbach’s α = .55–.76) measured in an adolescent population.Central coherence and cognitive flexibility: Computergestütztes Kartensortierverfahren (CKV) [49] is the German version of the Wisconsin Card Sorting Task which measures cognitive flexibility and set-shifting ability. So far, there is no information about the reliability of this measure, but the split-half reliability of the English version is excellent (.90 ≤ r ≤ .95) [50]. The Rey Complex Figure Test and Recognition Trial (RCFT) [51] is a neuropsychological drawing task measuring gestalt processing. The drawing will be rated by a psychologist according to the scoring system from Booth [52] in order to calculate a central coherence score. The inter-rater reliability ranges from .71 to .97.Emotion recognition: The Frankfurter Test und Training of Facial Affect Recognition (FEFA-2) [53] is a computerized neuropsychological task testing facial affect recognition showing good psychometric properties (Cronbach’s α ≥ .91). The Toronto-Alexithymia Scale-26 (TAS-26) [54] is a self-rating questionnaire measuring alexithymia, a personality trait characterized by the inability to identify and describe emotions experienced by oneself or others, which is often impaired in people with AN [55, 56]. Internal consistency examined in an adolescent sample is moderate to good (Cronbach’s α = .67–.84) [54].Personality: The subscales harm avoidance, persistence and self-directedness of the Junior Temperament and Character Inventory (JTCI) [57] will be used to measure perfectionism and rigid personality traits. The three subscales of this self-rating questionnaire for adolescents showed good internal consistency (Cronbach’s α = .82–.86).Social media use: We constructed a self-rating questionnaire based on questions of the Pro-Anorexia Website Survey (PAWS) [58] to assess the frequency of social media use and the influence on ED behavior prior and after the intervention.Motivation: Motivation for change will be measured with the Anorexia Nervosa Stages of Change Questionnaire (ANSOQC) [59], a self-rating questionnaire with good reliability (Cronbach’s α ≥ .76) and validity for adolescents [60]. The Psychotherapy Motivation Questionnaire (FPTM-40) [61] measures the motivation to attend psychotherapy from a patient’s perspective. The internal consist of this measure is acceptable (Cronbach’s α = .70).Treatment acceptability: Treatment acceptability will be assessed with the Questionnaire to Assess Treatment (FBB) [62], which has good internal consistency (therapist version: Cronbach’s α = .88; patient version: Cronbach’s α = .83). The therapeutic alliance as possible mediating factor will be with the self-rating questionnaire Therapeutic Alliance Scale for Children (FTB-KJ) [63]. The measure has good internal consistency (therapist version: Cronbach’s α = .83; patient version: Cronbach’s α = .82). Both, FBB and FTB-KJ will be filled in by the participants and the therapists.Treatment process and feasibility of the intervention: The Session Evaluation Questionnaire (SEQ-d [64] will be used in the MANTRa group for systematic examination of the treatment process. The SEQ-d will be completed after each session by the therapist and the patient (not listed in Fig. 1). The internal consistency of the English version is excellent (Cronbach’s α = .80–.92). There is no data about reliability or validity for the German version so far [65]. Additionally, we will use qualitative methods to gain insights into the patients’ and therapists’ personal experiences with the MANTRa therapy and to further improve the workbook: For example, we will analyze parts of the therapy content (formulation and goodbye letters, virtuous and viscous flower) by means of qualitative analyses. In addition, we will ask patients about their experiences with the MANTRa treatment program at T2 using 5 open-ended questions and we will interview the MANTRa therapists with semi-structured interviews. Qualitative data will be analyzed in NVivo software [66].
